### Concomitant medication

Emollient therapy and mild-moderate topical corticosteroids will be permitted throughout the trial. Investigator-directed use of potent/super potent topical corticosteroids as ‘rescue’ therapy can be used if necessary, with the volume used recorded at study visits to evaluate any potential confounding effect.

Systemic therapies that are likely to have efficacy in PPP or to compound the immunosuppressive effects of upadacitinib are prohibited. If treatment with these is essential, the participant must notify the study team and they will be withdrawn from the trial.

Guidance from the clinical trials facilitation and co-ordination group will be followed regarding effective forms of contraception during the trial.

### Data collection and management

All outcome assessments of PPP will be assessed by an independent assessor blinded to the patient participant’s position on the trial pathway (ie, screening/receiving treatment/follow-up visit) to minimise bias. They will not be involved in other aspects of the trial (eg, recruitment, qualitative interviews). There should be no need for unblinding of assessors as safety concerns will be addressed by the unblinded research team members.

A visit window of 3 days either side of the scheduled visit will be allowed. In the event that a visit falls outside the target visit window of +3 days, the visit should be scheduled as soon as possible, and the data should be entered into the intended visit. All visits will be carried out in person. In exceptional circumstances where a patient is unable to attend a study visit, a virtual visit will be carried out.

Data will be collected using a paper case report form and stored securely in an electronic data management system (CAPTURE). Personal information stored within CAPTURE that could identify individuals will remain strictly confidential. Access to the information will be restricted at all times to researchers with clear purpose or need to access it. All data held within CAPTURE is processed in accordance with the Data Protection Act 2018 and UK General Data Protection Regulation (GDPR).

Should a participant decide to withdraw from the trial, all efforts will be made to report the reason for withdrawal as thoroughly as possible and they will be encouraged to continue to provide outcome data. All data collected to date will be retained.

We will seek participant consent in the informed consent form for their de-identified study data to be shared with research collaborators running other research studies in our organisation and in other organisations.

### Statistical analysis

Baseline characteristics will be summarised by using suitable measures of central tendencies. For continuous data, means/medians and SD/IQR will be reported depending on the data distribution, and frequencies with proportions will be reported for categorical data. The primary feasibility outcomes will be reported as proportions with a 95% CI. No formal hypothesis testing will be conducted as this is a feasibility study. A detailed statistical analysis plan has been written for the analysis approach.

The mean change in PP-PASI at week 8 for the treatment arm will be estimated with a 95% CI. This analysis will follow an intention-to-treat principle and include all participants with a non-missing outcome, regardless of how much treatment was received. Every effort will be made to reduce missing data. No imputation will be made for missing data for this feasibility study. Patterns of missingness will be explored and its relationship to the outcome described.

For the comparison with the historical control data, the analysis model will be a linear (Gaussian) mixed effect model, using PP-PASI scores from weeks 1/4/8, adjusted for baseline PP-PASI. This model will include a random effect for participant and fixed effects for time, time-by-treatment group interaction and baseline PP-PASI.

Statistical analysis will be undertaken according to the latest guidelines on the use of historical controls.^16^ The trial protocol is matched to the APRICOT where possible (inclusion/exclusion criteria, study methods, measurements).^16^ The access to contemporaneous, patient-level data will enable adjustment for patients’ covariates and the involvement of a blinded assessor will mitigate the inherent risk of bias associated with an open label, single-arm design. Sensitivity analyses exploring the use of inverse probability of treatment weighting to adjust for any observed differences between the treatment cohort and the historic controls will be conducted if unbalance is observed between the treatment cohort and the historic controls to ensure the robustness of results.^34^ Given the change to the APRICOT exclusion criteria to address the recent MHRA guidance (ie, exclusion of patients over the age of 65 unless there are no suitable alternatives), a sensitivity analysis based on the subset of patients across APRICOT and JAKPPPOT who would have been eligible for both trials will be conducted if required.^9^ If previous placebo APRICOT participants are recruited into the JAKPPPOT study, an additional sensitivity analysis will be conducted, excluding their data from the APRICOT placebo cohort.

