### Outcomes

#### Primary outcomes

The following outcomes will be assessed after 24 months of recruitment, or when the recruitment target of 20 participants is achieved (whichever occurs first):

Overall proportion of potential participants identified who enrolled in the trial, termed the ‘recruitment rate’.‘Potential participants identified’ is defined as those who have direct contact with the research team.Overall proportion of participants achieving ‘good adherence’ (proportion of days covered >80%) during the trial.‘Proportion of days covered’ is defined as the total medication taken during the 8-week trial period as a proportion of the total medication dispensed.Overall proportion of participants who view JAK inhibitor therapy in PPP to be ‘acceptable’.Acceptability will be measured based on responses to the following question at the end of the 8-week treatment period: ‘Overall, how acceptable was taking upadacitinib to you?’A 5-point Likert scale will be used, with answers dichotomised into acceptable (acceptable/completely acceptable) or unacceptable (completely unacceptable/unacceptable/neutral)

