#### Exploratory outcomes

The following outcomes are assessed after 24 months of recruitment, or when the recruitment target of 20 participants is achieved (whichever occurs first):

Evaluation of trial recruitment diversity and inclusion.Participant demographics will include age, sex, ethnicity and socioeconomic background.Accuracy of disease severity assessments of photographs compared to in-person assessments.PP-PASI and Palmoplantar Pustulosis-Investigator Global Assessment (PPP-IGA) grading of photographs will be compared with in-person disease severity assessments.Overall mean change in total pustule count over the 8-week treatment period, compared to baseline adjusted for baseline total pustule count.Placebo control data from the APRICOT (2015–2020, n=31 with complete data) will be used as a comparator.Overall mean change in fresh pustule count over the 8-week treatment period, compared to baseline adjusted for baseline fresh pustule count.Placebo control data from the APRICOT (2015–2020, n=31 with complete data) will be used as a comparator.Overall proportion of participants achieving clearance of PPP over the 8-week treatment period.Clearance will be defined as a PPP-IGA of 0/1.Placebo control data from the APRICOT (2015–2020, n=31 with complete data) will be used as a comparator.Overall mean change in chronic plaque psoriasis severity (if applicable) over the 8-week treatment period, adjusted for baseline chronic plaque psoriasis severity.Severity will be assessed using the PASI.^23^Placebo control data from the APRICOT (2015–2020, n=16 with complete data) will be used as a comparator.Overall mean change in participants’ symptoms and quality of life over the 8-week treatment period, adjusted for baseline. Dermatology Life Quality Index, Patient Global Assessment and European Quality of Life 5 Dimensions 5 Level Version (EQ5D-5L) will be used to assess participants’ symptoms and quality of lifePlacebo control data from the APRICOT (2015–2020, n=31 with complete data) will be used as a comparator.Overall proportion of participants achieving a 50% reduction in PP-PASI score (PPPASI50) over the 8-week treatment period, compared to baseline (visit 1).Placebo control data from the APRICOT (2015–2020, n=31 with complete data) will be used as a comparator.

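### The week-8 PP-PASI mean is called intention-to-treat but uses observed cases only, and follow-up after mandatory withdrawal is unclear, so it and possibly acceptability may look too favourable

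*Protocol article*

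**What the plan says.** Under Statistical analysis, the treatment-arm mean change in PP-PASI at week 8 is described as following the intention-to-treat principle. The analysis will "include all participants with a non-missing outcome, regardless of how much treatment was received". The same paragraph adds "No imputation will be made for missing data for this feasibility study" and "Patterns of missingness will be explored and its relationship to the outcome described". The next paragraph gives a different analysis for the comparison with APRICOT: a linear mixed model on the scores at weeks 1, 4 and 8, adjusted for baseline.

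Under Concomitant medication, systemic therapies likely to work in PPP, or to add to the immunosuppression, are prohibited. The rule is: "If treatment with these is essential, the participant must notify the study team and they will be withdrawn from the trial". Under Data collection and management, a participant who decides to withdraw is treated differently: "they will be encouraged to continue to provide outcome data". The section also states "All data collected to date will be retained".

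Acceptability, a primary outcome, rests on one post-treatment answer: "Acceptability will be measured based on responses to the following question at the end of the 8-week treatment period". PPPASI50 is exploratory: "Overall proportion of participants achieving a 50% reduction in PP-PASI score (PPPASI50) over the 8-week treatment period". The Sample size rationale says that the treatment-arm PP-PASI reduction will inform the definitive trial's sample size.

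**The concern.** Including people whatever treatment they took is only half of an intention-to-treat analysis. The other half is having outcomes for everyone who started. Here the week-8 mean is an observed-case analysis, and one of the routes out of the trial can be linked to the outcome: needing another systemic drug may mean that the disease was not controlled. If such participants have no week-8 score, the single-arm mean describes those who stayed. It also ignores the week 1 and week 4 scores of those who left, although the plan's own mixed model would use them.

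For acceptability, the article does not say how a participant without an answer counts. If only respondents are counted, those who stopped because of side effects or lack of benefit drop out of the denominator. A progression category is at stake, because Table 2 calls the domain feasible above 80%, and qualitative findings are used to settle intermediate results.

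**Working it through.** **Inputs.** n = 20, mean baseline PP-PASI 17.8 and SD of change 7.32 (Sample size rationale). Acceptability bands: below 20% non-feasible, 20–80% intermediate, above 80% feasible (Table 2). The document gives no dropout rate, so 1 to 4 missing of 20 is an assumption used to show the range.

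**The plan's own precision figure.** Half-width = t(0.975, n−1) × SD/√n. With n = 20: 2.093 × 7.32/√20 = 3.43 PP-PASI points, as stated. The figure therefore assumes that all 20 are observed. With 19, 18, 17 and 16 observed it becomes 3.53, 3.64, 3.76 and 3.90.

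**Week-8 mean change.** If m of 20 are missing, the observed-case mean overstates the mean over all 20 by

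(m/20) × (mean improvement in observed − mean improvement in missing).

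Assume that observed participants improve by 8.9 points (half of 17.8):

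- Missing participants improve by 0: m = 1 gives 1/20 × 8.9 = 0.45 points; m = 4 gives 4/20 × 8.9 = 1.78 points.
- Missing participants improve by 4.45: m = 1 gives 1/20 × 4.45 = 0.22 points; m = 4 gives 4/20 × 4.45 = 0.89 points.
- Missing participants improve as much as observed ones: no bias.

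**Acceptability.** For each m, take the smallest number of acceptable answers that exceeds 80% of respondents. Compare it with the same number over all 20, with no answer counted as not acceptable:

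| Missing | Respondents only | All 20 |
|---|---|---|
| 1 | 16/19 = 84.2% (feasible) | 16/20 = 80.0% (intermediate) |
| 2 | 15/18 = 83.3% (feasible) | 15/20 = 75.0% (intermediate) |
| 3 | 14/17 = 82.4% (feasible) | 14/20 = 70.0% (intermediate) |
| 4 | 13/16 = 81.3% (feasible) | 13/20 = 65.0% (intermediate) |

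These counts were chosen to sit at the boundary. They show how few participants can decide the category, not how often that will happen.

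**PPPASI50.** With an illustrative 10 responders, the observed-case figures are 10/19 = 52.6%, 10/18 = 55.6%, 10/17 = 58.8% and 10/16 = 62.5%, against 10/20 = 50% when missing counts as non-response.

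**Follow-up wording.** Concomitant medication imposes withdrawal from the trial, not only from study drug. The encouragement to go on giving outcome data is conditional on the participant's own decision to leave. It is not expressly confined to that case, so the text neither covers nor excludes those withdrawn because they need prohibited therapy.

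**The case against.** A reader might infer that treatment failures are simply dropped and that acceptability, PPPASI50 and PP-PASI are all biased upward. The documents do not support that, for these reasons:

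- Data already collected are kept, continued outcome data are encouraged from participants who decide to leave, observed outcomes count whatever treatment was taken, and missingness will be described.
- Withdrawal under the concomitant-medication rule need not mean treatment failure. The prohibition also covers drugs that add to immunosuppression, and potent topical rescue is allowed without withdrawal.
- Acceptability, PPPASI50 and PPP-IGA 0/1 are defined as proportions of participants, which can be read as keeping all 20 in the denominator. The no-imputation sentence stands in the paragraph on mean PP-PASI change, and the unseen analysis plan may settle the denominators.
- The effect size against APRICOT comes from a likelihood-based mixed model. It keeps participants who have a week 1 or week 4 score and is valid if data are missing at random.
- The APRICOT controls are described as 31 with complete data, so the net direction in between-group contrasts is uncertain.
- PPPASI50 and PPP-IGA 0/1 are exploratory and not progression criteria. An intermediate acceptability result does not stop progression, and the trial steering committee reviews all recommendations.

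All of this stands, and it limits the point. It does not remove it. The observed-case rule for the single-arm week-8 mean is stated, not left open, and that mean is named as an input to the next trial's sample size. A domain called feasible on respondents alone would also not need the qualitative findings that settle an intermediate result.

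**Conclusion.** The point holds in a limited form. The week-8 treatment-arm mean carries an intention-to-treat label but is an observed-case estimate, and the text is unclear on whether outcomes are sought from participants withdrawn for prohibited therapy. If missingness is related to poor response or intolerance, that mean is likely to be too favourable: by 0.22 to 1.78 points in the scenarios above, which rest on assumed improvements and 1 to 4 missing of 20. The same direction is likely for acceptability, PPPASI50 and PPP-IGA 0/1, but only if respondents alone are counted. For acceptability, one missing failure of 20 is enough to change the category. Upward bias is likely under these conditions but not shown, and its actual size cannot be derived from the document.

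**What to change.** 1. Reconcile Concomitant medication, Data collection and management, and Statistical analysis on whether outcome data are sought from participants withdrawn for prohibited systemic therapy, leaving the clinical rule itself unchanged. If such scores are collected, say whether they enter the week-8 mean.
2. Estimate the week-8 treatment-arm mean change from the weeks 1/4/8 mixed model already planned, and show the observed-case mean as a sensitivity analysis. A participant with no score after baseline still adds nothing to the model, so report how many there are.
3. Report acceptability over all who took at least one dose, with no answer counted as not acceptable, next to the respondents-only figure. Call the domain feasible without qualitative review only if both exceed 80%. With 20 dosed, that means at least 17/20 = 85%.
4. For PPPASI50 and PPP-IGA 0/1, report a non-responder analysis that counts missing scores and scores after prohibited systemic therapy as non-response. Otherwise benefit from another drug could be credited to upadacitinib. Apply the same rule to the APRICOT controls, and show the observed-case figures alongside.

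The cost is a few sentences of analysis text, access to the APRICOT placebo participants without complete data for item 4, and possibly some week-8 assessments of withdrawn participants, depending on item 1. The downside is that counting missing as failure is conservative when data are missing for unrelated reasons, which is why both figures should be shown.

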#### Secondary outcomes

The following outcomes will be assessed after 24 months of recruitment, or when the recruitment target of 20 participants is achieved (whichever occurs first):

Total number of potential identified participants who have contact with the research team.Speed of participant identification (participants identified/month).Speed of participant recruitment (participants identified/month).Total number of ineligible participants.Reasons for ineligibility.Recruitment of 20 participants within 24 months.Overall mean change in Palmoplantar Pustulosis-Psoriasis Area and Severity Index (PP-PASI) over the 8-week treatment period, adjusted for baseline PP-PASI.^22^Placebo control data from the APRICOT (2015–2020, n=31 with complete data) will be used as a comparator.

The following outcome is assessed at the end of each phase of the QRI approach (new phase for every 20 eligible patient participants approached throughout the trial):

Change in recruitment rate with each phase of the QRI approach.

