### Sample size rationale

We will aim to recruit 20 participants, in keeping with other published feasibility studies.^24 25^ Over a 24-month recruitment period, we anticipate approaching a total of around 100 potentially eligible individuals. Based on previous experience, we anticipate that the actual recruitment rate would be no less than 20%, so this would provide us with at least 20 participants.

With 100 approached participants, if 20 (20%) are recruited into the trial, this would allow us to estimate the 95% CI for the recruitment rate with precision of at least ±8%. Assuming 75% of participants adhere to treatment at least 80% of the time (as observed in APRICOT), a sample size of 20 participants would allow us to estimate ≥80% treatment adherence with a 95% CI: 51% to 91%. With 20 participants on treatment, JAKPPPOT will estimate a PPPASI50 in the JAK inhibitor arm with precision of at least ±3.43 PP-PASI points. This is based on figures derived from the APRICOT (mean baseline PP-PASI: 17.8; SD for the PP-PASI change at 8 weeks in active arm: 7.32).^16^ A PPPASI50 is an outcome that has been analysed as a primary/secondary endpoint in several PPP trials and was described as ‘treatment success’ during patient and public involvement (PPI) discussions with people with PPP.^26^ The PP-PASI reduction in the treatment arm will inform the sample size calculation for a larger definitive trial.

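### The historical-control model holds the baseline PP-PASI slope constant over weeks 1, 4 and 8, so the week-8 difference may be mis-adjusted if the cohorts differ at baseline and that slope changes across visits

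*Protocol article*

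**What the plan says.** The Statistical analysis section of the protocol article specifies the comparison with historical controls as a "linear (Gaussian) mixed effect model, using PP-PASI scores from weeks 1/4/8, adjusted for baseline PP-PASI". It then names the terms: "This model will include a random effect for participant", together with "fixed effects for time, time-by-treatment group interaction and baseline PP-PASI". The group effect may differ by week. Baseline enters only as a main effect, and no baseline-by-time term is listed.

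The model serves a secondary outcome, the mean PP-PASI change "over the 8-week treatment period, adjusted for baseline PP-PASI". The treated group has a target of 20 participants. For the other group the article says: "Placebo control data from the APRICOT (2015–2020, n=31 with complete data) will be used as a comparator". The Comparator section gives this comparison the purpose of indicating an effect size for the sample size of a definitive RCT.

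On imbalance, the Statistical analysis section says that patient-level data will allow covariate adjustment. It plans inverse probability of treatment weighting as a sensitivity analysis, to be run if the cohorts are seen to differ. It also mentions a detailed statistical analysis plan, which is not available here.

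**The concern.** One baseline coefficient fitted to three visits is an average over those visits. If baseline predicts week 1 strongly and week 8 less strongly, which is plausible because correlation usually weakens with time, the average is too steep for week 8. The week-8 comparison then subtracts too much for any baseline difference between the groups.

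In a randomised trial the expected baseline difference is zero, so this error averages out. Here 20 new patients are set against 31 placebo patients from a trial run in 2015–2020, and nothing guarantees a zero expected difference. Baseline PP-PASI is also the only covariate named in the main model, so the form of that adjustment matters.

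The week-8 difference is the natural effect size to carry into the RCT sample size. A systematic error in it would pass into that calculation.

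**Working it through.** **Inputs from the article.** Visits at weeks 1, 4 and 8; one participant random effect; 20 treated and 31 control patients; "mean baseline PP-PASI: 17.8; SD for the PP-PASI change at 8 weeks in active arm: 7.32".

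**Inputs assumed.** The article gives no visit-specific slopes, no between-cohort baseline difference, no baseline SD and no variance components. I assume a baseline SD of 9, a participant SD of 4.5 and a residual SD of 4. Slopes are common to both groups, week is categorical and visits are complete.

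**The plan's own figure.** The article states no precision for the historical comparison. Its single-arm figure reproduces: t(0.975, 19 df) × 7.32/√20 = 2.093 × 1.637 = 3.43 points. For scale, a plain 20 v 31 difference with the same SD has half-width t(0.975, 49 df) × 7.32 × √(1/20 + 1/31) = 2.010 × 7.32 × 0.287 = 4.2 points.

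**Step 1: the bias formula.** Let b1, b4 and b8 be the true baseline slopes at the three visits, and D the baseline difference (treated minus control). With complete visits and a random intercept, the single fitted slope estimates the mean of b1, b4 and b8. The fitted week-8 contrast is the raw week-8 difference minus that mean times D, whereas the correct adjustment is b8 times D. Hence

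bias at week 8 = (b8 − mean(b1, b4, b8)) × D.

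It is zero if D = 0 or if the three slopes are equal.

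**Step 2: a yardstick for D.** With baseline SD 9, the chance standard error of D is 9 × √(1/20 + 1/31) = 2.6 points, even if both cohorts came from the same population. I use D = 2.6 and D = 4.

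**Step 3: the numbers.**

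| Assumed slopes, weeks 1/4/8 | b8 − mean slope | Bias, D = 2.6 | Bias, D = 4 |
|---|---|---|---|
| Equal at all visits | 0 | 0 | 0 |
| 0.9/0.8/0.7 | 0.7 − 0.8 = −0.1 | −0.26 | −0.40 |
| 0.9/0.7/0.5 | 0.5 − 0.7 = −0.2 | −0.52 | −0.80 |
| 0.95/0.6/0.35 | 0.35 − 0.633 = −0.283 | −0.74 | −1.13 |

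A negative bias exaggerates benefit. If the treated cohort starts lower, D is negative and benefit is understated by the same amount.

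**Step 4: simulation check.** With 20 v 31 patients, D = 4 and 20,000 runs per setting, the listed model gave biases of −0.43, −0.82 and −1.14 for the three falling-slope rows. With a separate baseline slope per visit, the bias was between −0.03 and 0.00. The SD of the estimate was 1.78 to 1.92 under the listed model and 1.79 to 1.80 with visit-specific slopes. In separate runs (6,000 per setting), coverage of the 95% interval under the listed model was 94.3%, 92.3% and 89.8%, against 94.6% to 94.9% with visit-specific slopes.

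**Step 5: consequence for an RCT sample size.** Required n is proportional to 1/effect². If the true difference were 4 points (assumed), an overstatement of 0.4 to 1.1 would give (4/4.4)² = 0.83 to (4/5.1)² = 0.62 of the size needed. At 6 points it would give (6/6.4)² = 0.88 to (6/7.1)² = 0.71.

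**The case against.** Several points count against making much of this.

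- **Nothing in the article shows that bias will occur.** Slopes and baseline difference are all assumed, and eligibility and measurements follow APRICOT where possible. A 4-point difference is about 1.5 chance standard errors (4/2.6). This stands, and it is why the point is conditional.
- **The plan anticipates imbalance.** Weighting that includes baseline PP-PASI would push D towards zero and remove most of the bias. This stands in part. The weighting is a sensitivity analysis, run only if imbalance is seen, and the main estimate does not change.
- **The stakes are limited.** The comparison is secondary and untested, and no progression criterion uses it. The Sample size rationale says the reduction in the treatment arm will inform the RCT, and the single-arm estimate does not use this model. This lowers the weight, but the Comparator section does give the historical comparison that role.
- **The unseen analysis plan may already contain the term.** That is possible. The article nevertheless states the model term by term, and that stated model can be improved.

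A reader might also argue that an effective drug weakens the link between baseline and week 8, and that the interaction deals with this. It does not. Such a slope would differ by group, and a baseline-by-week term still assumes equal slopes in both groups. Suppose the week-8 slopes are 0.3 (treated) and 0.8 (control), D = 4, and there is no effect at the control mean. The average effect in the treated is (0.3 − 0.8) × 4 = −2.0. The pooled week-8 slope is (19 × 0.3 + 30 × 0.8)/49 = 0.61, so the visit-specific model gives 0.3 × 4 − 0.61 × 4 = −1.2, which is neither −2.0 nor the zero effect in a control-like population. The case for the change rests on slopes that vary by visit, not by group.

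**Conclusion.** The point holds conditionally. As listed, the model fixes one baseline slope for three visits, and in a non-randomised comparison the week-8 difference is biased if two things are both true: the cohorts differ at baseline, and the slope changes across visits.

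A reader might infer that any baseline difference mis-adjusts week 8, or that the plan will overstate benefit. The documents support neither. Constant slopes give no bias at any baseline difference, and the direction follows the sign of a difference that is not yet known.

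Under the assumed slopes the size ranges from about 0.3 to 1.1 PP-PASI points, roughly 15% to 60% of a standard error of about 1.8 (0.26/1.8 to 1.13/1.8). That is below the sampling error of the comparison, but it would be systematic and is easily avoided. I rate it a minor-to-moderate improvement to a secondary estimate.

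**What to change.** Add a baseline PP-PASI-by-week interaction, with week as a category, to the stated mixed model. Carry the same term into the weighted and subset sensitivity versions, and report the week-8 group difference from this model. If the full analysis plan already has the term, only the article's description needs aligning.

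The cost is one line of specification and two degrees of freedom. It uses data already scheduled for collection. In the simulations the SD of the estimate was essentially unchanged or slightly smaller, and if the slopes turn out equal almost nothing is lost. The term does not handle a baseline slope that differs between treated and control patients, and should not be described as doing so.
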